***Antibody levels against CS (full-length and peptides other than repeat)***

Standardized ELISA procedures established in the Clinical Immunology Laboratory to measure antibodies full-length recombinant CS protein will be performed using commercially available secondary antibody IgG1 reagents. Full-length recombinant PfCS will be GMP protein containing the full-length N- and C-terminal domains plus 19 NANP and 3 NVDP amino acid repeats from the 3D7 strain of *P. falciparum*.

***Humoral assays to determine isotype, affinity, and epitope specificity***

Human isotypes IgG1, IgG2, IgG3, and IgG4 against PfCS repeat peptide (40-mer) and full-length recombinant CS protein will be performed using commercially available secondary antibody isotype reagents. Affinity and avidity measurements will be conducted using standardized procedures using the Attana 200 instrument for analysis of molecular interactions from whole sera. The Attana 200 instrument is a dual channel, label-free, temperature controlled, continuous-flow system for automated determination of avidity and affinity of antibody to CS repeat peptides and to full-length recombinant CS protein. This instrument uses Quartz Crystal Microbalance (QCM) technology that allows for simultaneous kinetic on and off-rate characterization from crude serum samples. Epitope mapping of sera samples from subjects will be first tested in modified ELISA using overlapping biotinylated peptides captured onto streptavidin-coated microtiter plates spanning the entire CS sequence with further characterization of epitopes analyzed for avidity. Statistical correlations will be made to assess correlation with protection and delay to infection using a combination of affinity/avidity with mapped epitopes.

***Cell-Mediated Immunity (CMI)***

The role of cell-mediated immunity in the protective response to malaria is poorly understood. In addition to assessment of humoral immune responses, assays to analyze the cellular immune responses will also be performed. The cell-mediated immune response will be assessed on thawed PBMCs by Intracellular Cytokine Staining (ICS) at GSK Biologicals or a validated laboratory designated by GSK Biologicals and by ELISPOT at Crucell laboratory.

***Detection of CS or HBs specific T-cells, ICS (Intracellular Cytokine Staining) technique***

Intracellular staining for cytokines (ICS) is a method providing information on the frequency of CD4+ and CD8+ T cells responding to the antigen and secreting molecules involved in immunity such as IFN- $\gamma$ , IL-2, TNF- $\alpha$  and CD40-L. The assay will be performed on thawed PBMCs. Briefly, PBMCs of the subjects are stimulated for 2 hours by the vaccine antigen (HBs and CS) and/or derived peptides. Then, intracellular block (Brefeldin A) is added to inhibit cytokine secretion for a subsequent overnight stimulation. The cells are then harvested and stained for cell surface markers (eg. CD4 and CD8), to identify specific sub-populations of T cells. Subsequently, the cells are fixed and then treated with a detergent such as saponin to permeabilize the cell membrane. The cells are then incubated with fluorescently labelled, cytokine-specific or activation marker-specific antibody that forms complexes with the cytokine in the

cytoplasm. The cytokine producing cells can then be detected by cytofluorometry. Results are expressed as a frequency of antigen-specific CD4+ or CD8+ T cells identified as expressing cytokine/marker upon the *in vitro* stimulation.

***Detection of CS or Ad35-specific T-cells, ELISPOT technique:***

The Human T-cell ELISPOT enumerates the number of IFN- $\gamma$  producing T cells. This assay has been validated at the GLP laboratory at Crucell. A 15-mer overlapping peptide pool spanning the CS protein of high purity and extensive quality control has been designed to elicit cytokine production of CS specific T cells. Briefly, PBMC are thawed and rested overnight. The next day, cells are counted, plated in ELISPOT plates and stimulated overnight with CS peptide pool (2  $\mu$ g/ml per peptide) or controls. After incubation, secreted IFN- $\gamma$  is detected with alkaline phosphate conjugated detection antibody and stained with BCIP/NBT. Plates are air-dried and spots are counted with and AID ELISPOT counter. Responses are reported as spotforming units/10^6 cells.

***Cytokine and chemokine measurement by Luminex Assay***

Assessment of cytokines and chemokines in *serum* by particle based cytokine assay (Luminex®) at time points listed in [Table 6](#). (Amended 09 June 2011)

Luminex® assays as standardized in commercially available kits (i.e. Invitrogen, Inc.) will be used to assess cytokine and chemokines in sera from subjects at predefined time points as indicated in the protocol. (Amended 09 June 2011) The assay will include those from a 30-plex kit for the simultaneous measurement of human IL-1 $\beta$ , IL-1RA, IL-2, IL-2R, IL-4, IL-5, IL-6, IL-7, IL-8, IL-10, IL-12 (p40/p70), IL-13, IL-15, IL-17, TNF- $\alpha$ , IFN- $\alpha$ , IFN- $\gamma$ , GM-CSF, MIP-1 $\alpha$ , MIP-1 $\beta$ , IP-10, MIG, Eotaxin, RANTES, MCP-1, VEGF, G-CSF, EGF, FGF-basic, and HGF. Depending upon the results from the microarray transcriptional analysis, additional cytokines may be tested and obtained from commercially available sources. Flexibility is one of the many advantages of the Luminex® xMAP® multiplex platform. Luminex® assays are easy to set up and run, using a procedure that is very similar to an ELISA. We will use the maximum number of beads in each Luminex® assay, so that data are collected from at least 100 events per bead region per target. Counting at least 100 events, compared to the 50 recommended by some manufacturers, leads to lower % CVs and more precise assays. Luminex® assays are subject to rigorous quality control and validation prior to release.

***Flow cytometry analysis for plasmablasts (FACS) and B cell ELISPOT***

Flow cytometry will be used to evaluate the frequency and phenotype of circulating antibody-secreting cells, specifically CD19+ CD38+ CD27+ plasmablasts at time points listed in [Table 6](#). Plasmablasts, released from germinal centers appear transiently in the blood for several days post immunization before they home to the bone marrow. This cell type is considered critical for humoral memory and the persistence of antibodies. Since they do not survive the freeze/thaw process, this particular FACS staining will have to be performed on fresh cells. Further, to enumerate CS-specific cells that actively secrete antibodies, B cell ELISPOT analysis will be performed.

## Gene expression profiling

### *Microarray Analyses*

Microarray analysis will be performed using a 3-step strategy that will use the vaccinees from cohort A to define signatures that correlate with the antigen-specific immune responses, and protective efficacy, and then test the predictive capacity of such signatures using the vaccinees in cohorts B and C.

Step 1: To identify gene signatures that correlate with immunogenicity and protection in a “Training set”, using vaccinees in “cohort A” (23 vaccinees per arm).

- Microarray analyses of PBMCs of 23 vaccinees per arm
- 23 vaccinees/arm x 2 arms x 14 time points (see [Table 6](#)) = 644 samples  
(Amended 09 June 2011)

In step 1, we will perform an intensive analysis of the kinetics of gene expression in all 46 vaccinees from cohort A to define the time point(s) at which the gene expression profiles best correlate with the ensuing antigen-specific antibody and T cell responses and protective immunity against malaria challenge. Gene expression analysis will be performed using the Affymetrix GeneChip Human Genome U133 Plus 2.0 Array. The analysis of gene expression data will be performed as described by Querec et al. [[Querec, 2009](#)].

Upon completion of cohort 1, there can be 2 possible outcomes:

1. Discontinuation of the study, for the reasons defined in the protocol. In this event, the primary end point of the systems biological analysis would have been to define signatures that correlate with antigen-specific immune responses and efficacy. A secondary end point would be to use a classification model such as the DAMIP model [[Querec, 2009](#)], a general-purpose optimization-based predictive modeling framework and computational engine, which is a very powerful supervised-learning classification approach in predicting various biomedical and biobehavioral phenomena. We will train the DAMIP model using cohort 1 to obtain an unbiased estimate of correct classification (between high and low immune responders, or between vaccinees who acquired the disease versus those who did not), within cohort 1.
2. Continuation of the study with analysis of cohorts B and C. This will allow us to test the predictive capacity of the signatures defined in cohort A, in an independent set of vaccinees in cohorts B and C. Therefore, in the following step 2, we will evaluate gene expression profiles on the time points identified as being most informative as per our analysis in step 1, with a view to determining whether such signatures can predict the antigen-specific antibody and T cell responses and efficacy, in the independent set of vaccinees in cohorts B and C. Therefore, we will first train the DAMIP model using trial 1 to obtain an unbiased estimate of correct classification, and then use cohort B as a blind test to predictive capacity of the signature.

Step 2: To test the predictive capacity of the signatures identified in cohort A using a “Test set 1” in cohort B

- Microarray analyses of PBMCs of 23 vaccinees per arm
- 23 vaccinees/arm x 2 arms x 4 time points = 184 samples for “Test set 1” (cohort B). We will only study the time points that were identified as being most informative in our analysis of cohort A.
- Total number of samples for microarrays in Test 1 (cohort B) = 184

If the signature defined in cohort 1 is capable of predicting the immunogenicity and efficacy in cohort B with high accuracy (e.g. >90%, as was the case with the yellow fever study [Querec, 2009], then we will further validate this signature using cohort C, as described below. If however, the predictive capacity is less than optimal, then we will treat cohorts A and B as a single dataset, by pooling the datasets from both cohorts, with a view to increasing the sample size and achieving greater statistical robustness in the analysis. Then we will test the predictive capacity of this signature (from the pooled cohort A and B analysis), using cohort C as a test set, as defined below.

**Step 3:** To test the predictive capacity of the signatures identified in cohort A (and cohort B) using a “Test set 2,” in cohort C

- Microarray analyses of PBMCs of 23 vaccinees per arm
- 23 vaccinees/arm x 2 arms x 4 time points = 184 samples for “Test set 2” (cohort C)
- Total number of samples for microarrays in Test 2 (cohort C) = 184

Total number of samples for microarrays = 690 (cohort A) + 184 (cohort B) + 184 (cohort C) = 1058

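### Appendix C calls the within-cohort-A classification accuracy unbiased, but the time points (and, on the plain reading, the genes) are chosen on the outcomes of the same 46 vaccinees, so it is biased upward

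*Protocol*

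**What the plan says.** The Microarray Analyses part of Protocol Appendix C sets out three steps. Step 1 uses cohort A as the training set: "23 vaccinees/arm x 2 arms x 14 time points". Its purpose is "To identify gene signatures that correlate with immunogenicity and protection in a" training set made up of these vaccinees. The time points are also chosen there, on everyone: "In step 1, we will perform an intensive analysis of the kinetics of gene expression in all 46 vaccinees from cohort A" is done "to define the time point(s) at which the gene expression profiles best correlate with the ensuing antigen-specific antibody and T cell responses" and protection after challenge.

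Two continuations follow. If the study stops after cohort A, a secondary end point of the systems-biology analysis is to classify high against low responders, or infected against uninfected vaccinees: "We will train the DAMIP model using cohort 1 to obtain an unbiased estimate of correct classification", within that cohort. If the study continues, the same property is claimed again: "we will first train the DAMIP model using trial 1 to obtain an unbiased estimate of correct classification". Only after that is the signature put to an independent blind test, on cohort B. Here cohort 1 and trial 1 can only mean cohort A. Cohort C is a second test set.

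The appendix does not describe how accuracy is estimated inside cohort A. It refers the gene-expression analysis to a cited publication.

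**The concern.** Accuracy estimated within a cohort is unbiased only if the subjects being classified played no part in building the rule. Here every cohort A subject's immune response and infection status helps decide which time points are used, and apparently which genes. Leaving a subject out when the classifier is fitted does not undo that. The text therefore asserts a property that its own procedure does not have.

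The stake is largest if the trial stops after cohort A. No independent vaccinees would then exist, and the within-cohort figure would be the only accuracy available for a signature of protection. That outcome is not remote: Section 5.4.4.2 gives a 40% probability of meeting the futility stopping criterion if the true increase in efficacy is 0%. If the trial continues, a fall in accuracy from cohort A to cohort B would be harder to interpret when the first figure had been labelled unbiased.

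**Working it through.** **The plan's own figures.** Training-set samples: 23 × 2 × 14 = 644, as Step 1 states. Table 6 shows 14 microarray draws. The appendix gives no numerical accuracy for cohort A, so there is none to reproduce.

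**Inputs from the protocol.** There are 46 subjects and 14 candidate time points. For infection status, Section 10.4 assumes a 50% attack rate in RRR and a 50% relative reduction in ARR. The overall rate is then (0.50 + 0.25)/2 = 0.375, or 46 × 0.375 ≈ 17 infected. A 23/23 split represents a median split into high and low responders.

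**Assumptions, because the protocol does not fix them.** The number of effectively independent features is 500 to 10,000. The signature has 1 to 20 genes, ranked by absolute t statistic. A diagonal linear discriminant stands in for DAMIP, one best time point is chosen, the correlation between time points is 0.5, and cross-validation is 10-fold. Each setting has 60 replicates, or 15 at 10,000 features (12 with correlated gene blocks).

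**Null simulation.** Expression has no relation to outcome, so a fair estimate with balanced classes should average 0.50. Entries are mean accuracy, with the share of runs above 90% in brackets. Classes are 23/23 with 14 time points.

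| Features | Genes | Genes and time point chosen on all 46, then cross-validated | Time point chosen on all 46, genes re-chosen in folds | Everything inside folds |
|---|---|---|---|---|
| 2,000 | 1 | 0.75 (0%) | 0.71 (0%) | 0.46 (0%) |
| 2,000 | 3 | 0.85 (13%) | 0.71 (0%) | 0.53 (0%) |
| 2,000 | 5 | 0.88 (27%) | 0.69 (0%) | 0.51 (0%) |
| 2,000 | 10 | 0.93 (85%) | 0.68 (0%) | 0.50 (0%) |
| 2,000 | 20 | 0.97 (98%) | 0.67 (0%) | 0.48 (0%) |
| 500 | 5 | 0.83 (8%) | 0.68 (0%) | 0.48 (0%) |
| 500 | 10 | 0.89 (42%) | 0.67 (0%) | 0.49 (0%) |
| 10,000 | 5 | 0.91 (53%) | 0.69 (0%) | 0.50 (0%) |
| 10,000 | 10 | 0.96 (100%) | 0.69 (0%) | 0.50 (0%) |

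In the fourth column the time point is the one with the best cross-validated accuracy. Choosing it instead by strength of correlation with outcome gives somewhat lower values, so the overall range for this route is about 0.63 to 0.71. The bias from time-point choice alone is therefore about 0.63 − 0.50 = 13 to 0.71 − 0.50 = 21 percentage points.

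A 17/29 split at 2,000 features gives similar results: 0.89 (5 genes) and 0.93 (10 genes) after selection on all 46, 0.71 with only the time point chosen outside, and 0.53 with everything inside the folds. Correlated gene blocks do not change the pattern. Classifying the training subjects with no cross-validation at all gives 0.76 to 0.98 in the balanced settings.

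**Cohort B.** The same null signatures average 0.49 to 0.54 in an independent cohort of 46. Exceeding 90% there needs at least 42 correct, since 0.9 × 46 = 41.4. The binomial probability P(X ≥ 42) is 2.6 × 10⁻⁹ at 50% accuracy and 1.0 × 10⁻⁵ at the 62.5% majority-class rate.

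**The case against.** The best defence has four parts.

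- **Unseen method.** The estimation method is delegated to a publication and, for the relation between immune response and efficacy, to the statistical analysis plan (Section 10.8.3). Either might repeat all selection inside the folds. This stands to the extent that an unstated nesting scheme is not a finding. It does not rescue the wording: the only selection the protocol describes is done on all 46, and cross-validating just the classifier afterwards leaves the bias in place.
- **Context.** The appendix labels cohort A a training set, and if the study continues the same sentence goes straight on to a blind test in cohort B. The endpoint is exploratory, and no primary or secondary endpoint, sample size or stopping rule depends on it. This stands in full and limits the weight of the point.
- **Simulation.** It uses a stand-in classifier and a single time point, whereas four time points go forward to cohort B. With unequal classes the chance baseline is also not 50%: always guessing the majority class scores 62.5% under Section 10.4. These choices affect the size of the bias, not its direction.
- **The stronger reading.** A reader might infer that a signature of pure noise would usually score above 90% in cohort A, or that the appendix's 90% figure cannot separate signal from noise. The documents support neither. Exceeding 90% requires genes chosen outside the folds, roughly 5 to 10 or more of them, and enough features; the protocol fixes none of these. With only the time point chosen outside, no null run exceeded 90%. The appendix also gives its 90% figure as an example for predicting in cohort B, where a null signature has practically no chance of reaching it.

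**Conclusion.** The claim of an unbiased estimate is wrong as written, in both places where it appears. Under no association and balanced classes, the time-point selection that the protocol explicitly performs on all 46 vaccinees raises apparent accuracy from about 0.50 to about 0.63–0.71. If genes are also chosen on all 46, which is the plain reading, it rises to about 0.75–0.97, and between 0% and 100% of null runs exceed 90%. Repeating every selection inside the folds brings the mean back to roughly 0.50.

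These sizes rest on the assumed number of features, signature size and classifier, with 12 to 60 replicates per setting. The direction does not depend on them. The consequence is confined to the cohort A figure of an exploratory analysis, and matters mainly if the study stops after cohort A. The cohort B and C tests stand.

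**What to change.** In Appendix C, require that any accuracy reported within cohort A come from a procedure in which time-point choice, gene selection and classifier training are all repeated inside every cross-validation fold. Ideally, add a permutation p-value that reruns the whole pipeline on permuted outcomes. Time points and signatures to be carried into cohort B can still be defined on all 46.

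Otherwise, delete the word unbiased in both places (study stops, study continues), label the cohort A figure as training (apparent) accuracy, and state that predictive accuracy comes only from cohorts B and C.

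The cost is wording, some computing time and a less favourable cohort A figure. No extra samples or subjects are needed.

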### ***Deep sequencing***

Deep sequencing (mRNA-Seq) is a technique using next generation sequencing technology to sequence and quantify mRNA samples. It is more sensitive than microarray analysis allowing to measure very small changes in gene expression. It is to do with analysis of transcription, not genetic testing. The Illumina Genome AnalyzerII uses clonal array formation and reversible terminator technology to generate 20-30 million short sequence reads per sample lane. These short sequences are aligned with the genome and counted to provide the numerical frequency of sequences in the library population. This technique reveals much more information about the transcriptome than the hybridization-based technologies. In addition to identifying transcripts and determining relative expression levels, sequencing the entire mRNA population uncovers novel transcripts and isoforms, alternative splice sites, information regarding gene promoters and rare transcripts. The experiments will be instructed by the results obtained from the microarray studies.

### **Determination of parasitemia**

Blood samples for smear and PCR will be taken during the challenge phase at the time points listed in Table 6. Detection and quantification of *P. falciparum* parasitemia will be made at the investigator’s sites according to laboratory SOPs.

## Appendix D Amendments and administrative changes to the protocol

| GlaxoSmithKline Biologicals
Clinical Research & Development
Protocol Amendment 1                                                                                                                                                                                                                                                                                                                                                                                                                                                                                                                                                                                                                                                                                                                                                                                                                                                                                                                                                                                                                                                                                                                                                                                                                                                                                                                                                                                                                                    |                                   |
|-----------------------------------------------------------------------------------------------------------------------------------------------------------------------------------------------------------------------------------------------------------------------------------------------------------------------------------------------------------------------------------------------------------------------------------------------------------------------------------------------------------------------------------------------------------------------------------------------------------------------------------------------------------------------------------------------------------------------------------------------------------------------------------------------------------------------------------------------------------------------------------------------------------------------------------------------------------------------------------------------------------------------------------------------------------------------------------------------------------------------------------------------------------------------------------------------------------------------------------------------------------------------------------------------------------------------------------------------------------------------------------------------------------------------------------------------------------------------------------------------------------------------------------------|-----------------------------------|
| eTrack study number and Abbreviated Title                                                                                                                                                                                                                                                                                                                                                                                                                                                                                                                                                                                                                                                                                                                                                                                                                                                                                                                                                                                                                                                                                                                                                                                                                                                                                                                                                                                                                                                                                        | 114460 (Malaria-068)              |
| IND number                                                                                                                                                                                                                                                                                                                                                                                                                                                                                                                                                                                                                                                                                                                                                                                                                                                                                                                                                                                                                                                                                                                                                                                                                                                                                                                                                                                                                                                                                                                       | BB-IND-14701        |
| Amendment number:                                                                                                                                                                                                                                                                                                                                                                                                                                                                                                                                                                                                                                                                                                                                                                                                                                                                                                                                                                                                                                                                                                                                                                                                                                                                                                                                                                                                                                                                                                                | Amendment 1                       |
| Amendment date:                                                                                                                                                                                                                                                                                                                                                                                                                                                                                                                                                                                                                                                                                                                                                                                                                                                                                                                                                                                                                                                                                                                                                                                                                                                                                                                                                                                                                                                                                                                  | 09 June 2011                      |
